### 2.14 Data collection, site monitoring, and adverse experience reporting

Standardized questionnaire and training of data collectors to be done by the PI to ensure reliability and validity of the study. Data collection will be done by the data collectors under supervision of the PI and CTU. Questionnaires will be checked for consistency and logical entries. Data entry will be done, and counter checked by the PI on regular intervals. Data collected will be kept confidential without identifiable information of patients who are identified by a number assigned. The hard copy forms will be retained in a secured location with the PI after data entry into computer software and will be kept as per hospital protocol.

### 2.15 Data Management

#### 2.15.1 Data Editing

Data editing will be done both by the data collector or PI at the time of data collection. The questionnaire will be checked for consistency, completeness, and logical entries. To obtain smooth data entry, PI will be carrying out another data editing after completion of data collection process. Data editing is a continuous process, at the completeness of form and then at the time of data entry and at end of data entry.

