### 2.3 Primary and secondary Outcome Measures

Primary outcome will be the time interval in hours from end of surgery till passage of flatus, which is reported subjectively by the patient. Patients will be instructed to make note of the time when flatus is passed first time after surgery. Secondary outcomes will be the postoperative interval until the first passage of stool in hours as well as postoperative hospital stay in days (Surgery to discharge).

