### 2.7 Handling of Study Interventions

Sugarless gum will be purchased in bulk after confirming the expiry date and will be kept at the Clinical Trial Unit (CTU) team, dispatching the required gums as per patients’ needs and request from the ward nurse, preferably one at a time. As the intervention is behavioral, it will not be suitable to blind/mask the study intervention.

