### 2.10 Randomization

After screening and eligibility, patients will be randomly allocated by 1:1 ratio to the Group A gum-chewing (Gum) or Group B control (No gum) groups using a computer-generated randomization sequence by the CTU at the Aga Khan University, which they will provide to the nurse/PI by telephone after patients’ admission in hospital. Patients will be followed from the time they reach the ward after surgery till their hospital discharge, which is usually 7 days.

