#### 2.15.2 Data Entry

Data will be entered twice. First entry will be done by the data entry operator and second will be done by PI. The data entry operator will be trained for data entry in terms of reading the filled data forms and its code book. The operator will be asked to enter data for 30 study participants under the supervision of the PI and the mistakes will be communicated. Both the entries will be checked by PI for consistency and errors will be corrected by referring to the forms.

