#### 2.15.3 Data cleaning

Data will be cleaned by checking missing values, double and un-realistic entries.

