#### 2.15.5 Quality Assurance

Quality of information gathered will be given priority and subsequently its integrity will be maintained. To ensure data quality, revisions and formatting of the instruments will be carried out to reduce error. PI will do the random checks for the completeness and consistency of data collection forms or request one of the study committee members to that. The data collection forms will be reviewed on daily basis by principal investigator for the purpose of good quality of data collection. Mistakes identified in this manner will be assessed immediately and measures will be taken to correct them. Training will be given to the data collectors to ensure that there are no problems with the quality of data collection.

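### A PI who may be told the allocation also edits, re-enters and reconciles a subjective primary outcome, and no limits are set for unrealistic times

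*Protocol article*

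**What the plan says.** All references are to the protocol article.

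**Knowledge of the arm.** The CTU generates the sequence and telephones the allocation after admission (section 2.10): "which they will provide to the nurse/PI by telephone". The treatment is open: "As the intervention is behavioral, it will not be suitable to blind/mask the study intervention" (section 2.7).

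**The outcome.** Section 2.3: "Primary outcome will be the time interval in hours from end of surgery till passage of flatus, which is reported subjectively by the patient". Patients are told to note the time themselves.

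**Who handles the data.**
- At collection (2.15.1): "Data editing will be done both by the data collector or PI at the time of data collection".
- After collection (2.15.1): "To obtain smooth data entry, PI will be carrying out another data editing after completion of data collection process".
- Entry (2.15.2): a data entry operator makes the first entry and the PI the second. Then: "Both the entries will be checked by PI for consistency and errors will be corrected by referring to the forms".
- Cleaning (2.15.3): "Data will be cleaned by checking missing values, double and un-realistic entries". No person and no limits are given.
- Review (2.15.5): "The data collection forms will be reviewed on daily basis by principal investigator". Mistakes found are to be corrected.

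Section 2.14 has the data collectors work under the PI and the CTU, and the PI keeps the paper forms. Patients are identified by a number, which sections 2.14 and 2.15.4 present as a confidentiality measure. Nothing in sections 2.14 or 2.15 hides the arm from whoever edits, reconciles or cleans.

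**The concern.** Section 2.7 explains why gum chewing cannot be masked. It does not explain why the handling of outcome data has to be open as well, and the plan assigns most of that handling to a person who may hold the allocation.

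The opening for bias comes from the kind of outcome. The article names no independent record against which a patient's flatus time can be checked. Whether a given time is logical, complete or realistic is therefore partly a judgement. The expected direction is on record too, since the article's title already states that gum reduces the risk of ileus. Someone who knows the arm could, without intending it, query a long time in the gum group more readily than the same time in the control group.

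The primary comparison is at stake. With 50 patients per arm, a handful of asymmetric queries or deletions could move it.

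**Working it through.** **1. Each step set against the safeguard stated for it**

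| Step | Who | Safeguard stated |
|---|---|---|
| Receives allocation (2.10) | Nurse or PI | None that keeps it from the PI |
| Edits at collection (2.15.1) | Data collector or PI | None against knowing the arm |
| Edits after collection (2.15.1) | PI | None against knowing the arm |
| Second entry and reconciliation (2.15.2) | PI | Errors corrected from the forms |
| Cleans unrealistic entries (2.15.3) | Not named | No limits given |
| Daily form review (2.15.5) | PI | None against knowing the arm |

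The only safeguard that bears on a recorded value is correction from the forms. It catches a time keyed differently from the paper. It does not act on what was put on the paper, on edits to the form, or on the choice of which times to question.

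**2. What the protocol lets one calculate**

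There is no figure for this point to reproduce. Section 2.4 expects 50 per arm on grounds of feasibility and gives no effect size, standard deviation or power. The size of any editing bias therefore cannot be derived, and what follows shows sensitivity only.

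**3. Scale of a trial with 50 per arm** (assuming two-sided alpha 0.05 and 80% power)

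- Difference in means: detectable standardised difference = √(2/50) × (1.96 + 0.84) = 0.2 × 2.80 = 0.56.
- Hazard ratio, if all 100 patients have the event: for 1.75, z = (√100 / 2) × ln 1.75 − 1.96 = 2.80 − 1.96 = 0.84, which gives power of 80%.

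**4. Illustration: arm-aware deletion with no true effect**

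Assumptions: 50 times per arm from the same lognormal distribution (log-SD 0.5), no censoring, the k longest gum-arm times struck out as unrealistic, no control time struck out, log-rank test at |z| > 1.96, and 20,000 runs. The log-rank test uses only the order of the times, so these rates do not depend on the lognormal shape. Section 2.13 names this test for length of stay. It is used here as a simple unadjusted stand-in for the flatus comparison.

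| Gum times struck out | False-positive rate | Of which favouring gum |
|---|---|---|
| 0 | 5.3% | 2.7% |
| 1 | 8.2% | 6.6% |
| 2 | 12.4% | 11.6% |
| 3 | 18.4% | 18.0% |
| 5 | 33.5% | 33.3% |

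**5. Illustration: times moved and not deleted**

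If k of 50 gum-arm times are each moved h hours earlier, the arm mean shifts by k × h / 50. For 5 times moved 12 h this is 5 × 12 / 50 = 1.2 h. For 10 times moved 24 h it is 10 × 24 / 50 = 4.8 h. The second case alters a fifth of the arm by a full day each and is extreme. None of these inputs comes from the protocol.

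**The case against.** The strongest reply has four parts.

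**The roles are shared.** A reader might infer that the PI always receives the allocation, controls every step that can change the primary value, and does the cleaning. The text supports none of these. Allocation goes to the nurse or the PI. Data collectors record the data, and either they or the PI edit at collection. An operator makes the first entry. Another committee member may do the random checks in section 2.15.5. Section 2.15.3 names no cleaner. This part stands, and the point is limited accordingly. What remains explicit for the PI is editing after collection, the second entry, reconciliation and daily review.

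**Bias would leave traces.** A reader might infer that any such bias could not be detected later. The documents do not say that. Patients make their own note of the time, the questionnaires are kept for five years, and no passage says that entries are overwritten. This also stands. However, the article does not say that the patient's note is kept as source, so tracing a change is not assured.

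**Editing may mean only a routine check.** Section 2.15.1 describes it as checking consistency, completeness and logic. That is a fair reading, and nothing says that the PI may change a flatus time on judgement. Equally, nothing limits what may be changed, and choosing which times to question is itself a judgement.

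**A condensed article leaves data-management detail elsewhere.** Range limits, the audit trail and database lock may well sit in a fuller document, and their absence alone would be no finding. But the article does set out who receives the allocation and who edits and reconciles. The concern is with that stated arrangement.

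It is also true that the larger source of bias may be unmasked patients timing their own flatus. Editing without the arm does not touch it.

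**Conclusion.** The concern holds as a possibility that the stated roles leave open. A PI who may know the arm edits, re-enters, reconciles and reviews a subjective primary outcome, and unrealistic times are to be cleaned without stated limits.

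Its size cannot be derived from the documents. The illustrations show that one to five one-sided deletions per 50 would raise the false-positive rate from about 5% to between about 8% and 33%. They rest on the assumption that deletions fall only on the longest gum-arm times. A reader might take these rates, or the hour shifts, as an estimate of the bias to expect, or as a sign that selective editing is planned. They are neither, and nothing in the protocol suggests intent.

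The change is a cheap improvement worth making before enrolment. The point does not show that the trial's result would be invalid without it.

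**What to change.** **Section 2.10.** Have the CTU telephone the allocation to the ward nurse only, which the present wording already allows.

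**Section 2.15.**
- Record the arm and gum adherence on a sheet separate from the outcome sheet. The CTU holds the arm code until database lock.
- Do post-collection editing, discrepancy resolution and cleaning of flatus and stool times on the arm-free file. Where the PI knows the arm, the existing data entry operator or the CTU does this work.
- Before enrolment, fix the range limits beyond which a flatus or stool time counts as unrealistic.
- Keep every original entry legible. After collection ends, change an outcome time only to match the original form.

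**Cost.** Some protocol wording, a split form, slightly slower query handling, and some operator or CTU time where tasks move from the PI. The CTU already generates the sequence and helps to supervise data collection.

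**Limits.** An arm-free file does not mask a PI who has learned the arm in some other way, which is why the reassignment of tasks matters. Bias from unmasked patients reporting their own times also remains.

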#### 2.15.2 Data Entry

Data will be entered twice. First entry will be done by the data entry operator and second will be done by PI. The data entry operator will be trained for data entry in terms of reading the filled data forms and its code book. The operator will be asked to enter data for 30 study participants under the supervision of the PI and the mistakes will be communicated. Both the entries will be checked by PI for consistency and errors will be corrected by referring to the forms.

#### 2.15.3 Data cleaning

Data will be cleaned by checking missing values, double and un-realistic entries.

#### 2.15.4 Data storage

Data collected will be kept confidential without identifiable information of patients who are identified by a number assigned. The hard copy forms will be retained in a secured location with lock and key mechanism with the PI after data entry into computer which also secured by username and password. The data will be available for AKU Ethical Review Committee on request and might be published in journal without disclosing any identifiable information of patients. Questionnaires will be stored for 5 years after the study is completed as per policy of the institute.

#### 2.15.5 Quality Assurance

Quality of information gathered will be given priority and subsequently its integrity will be maintained. To ensure data quality, revisions and formatting of the instruments will be carried out to reduce error. PI will do the random checks for the completeness and consistency of data collection forms or request one of the study committee members to that. The data collection forms will be reviewed on daily basis by principal investigator for the purpose of good quality of data collection. Mistakes identified in this manner will be assessed immediately and measures will be taken to correct them. Training will be given to the data collectors to ensure that there are no problems with the quality of data collection.

#### 2.15.6 Study Modification/Discontinuation

The study can be modified or discontinued at any time by the CTU, ERC or the DSMB as part of their duties to ensure that research subjects are protected.

## 3. Ethical Considerations

This protocol is exempted from Ethical review at this stage however all the required approvals will be taken from the ethical review committee before starting the study.

### 3.1 Informed Consent

Informed consent will be taken from the patient as per routine protocol before the arthroplasty procedures in the hospital. Research objectives, methodology, risks, and benefits will be explained in detail. Consent will only be taken by the primary investigator at his clinic or the surgical resident on call after patient’s admission in hospital, as per routine care.

### 3.2 Subject Confidentiality

All laboratory specimens, evaluation forms, reports, video recordings, and other records that leave the site will be identified only by the Study Identification Number (SID) to maintain subject confidentiality. All records will be kept in a locked file cabinet. All computer entry and networking programs will be done using SIDs only. Clinical information will not be released without written permission of the subject, except as necessary for monitoring by IRB, the FDA, the NINDS, the OHRP, the sponsor, or the sponsor’s designee.

## 4. Dissemination of research findings

Publication of the results of this trial will be governed by the policies and procedures developed by the Executive Committee. Any presentation, abstract, or manuscript will be made available for review by the ERC and CTU prior to submission.
